#### Baseline data

Sociodemographic data: age, gender, usual residence, marital status, smoking, alcohol use, usual residency.Number of falls in the previous years, number and type of fractures.Comorbidities and medications.Appetite using the 4-item Simplified Nutritional Appetite Questionnaire.^39^Cognition will be assessed using the 10-item Abbreviated Mental Test Score.^40^Functional status: Barthel score will be collected from each participant at baseline.^41^Quality of life will be measured using EQ-5D-5L^42^ and ICECAP-O.^43^Frailty assessment tools: six tools will be used to assess frailty.Fried Frailty Index^44^: frailty measured by the presence of three or more of self-reported weight loss, exhaustion, low physical activity and measured slow walk time over 4 m (<0.8 m/s) and weak grip strength using a dynamometer according to a standardised protocol (maximum value will be recorded).^45^FRAIL scale: self-reported scale with five questions on fatigue, resistance, ambulation, illness and loss of weight.^21^Study of Osteoporotic Fracture (SOF) Criteria for Frailty assesses three components: weight loss, inability to do stand-up from a chair five times and self-reported lack of energy.^17^CFS: a subjective clinical evaluation by a healthcare professional matching the patient to one of nine descriptors, and figures in the domains of mobility, energy, physical activity and function.^46^PRISMA-7: a brief 7-item self-reported questionnaire.^47^electronic Frailty Index: derived from clinical data based on a count of 36 potential deficits.^48^Sarcopenia will be assessed using two methods: the 5-item questionnaire used as a screening tool for sarcopenia (SARC-F), and the European Working Group on Sarcopenia in Older People (EWGSOP) criteria.The SARC-F was recently developed and validated to screen for sarcopenia in clinical practice.^49^ It asks about strength, ambulation (walking independence), standing up from a chair, stair climbing and history of falls. This tool has been recommended to identify older people for further diagnostic evaluation for sarcopenia.^50 51^The EWGSOP criteria are the gold standard assessment for sarcopenia^52^ and have recently been updated.^53^ They use the presence of both low muscle function (grip strength and walking speed) and low muscle mass for the diagnosis of sarcopenia. Walking speed and grip strength will have already been measured in the assessment of frailty. Muscle mass will be measured using bioelectrical impedance, a simple, non-invasive technique, where electrodes at the wrist and ankle enable a small current (800 μA) to pass through the body at a range of frequencies and impedance is measured over seconds. This allows body composition to be estimated to derive skeletal muscle index (SMI, skeletal muscle mass divided by height squared) values.^54^ We will use published cut-off values for low SMI of <8.87 and <6.67 kg/m^2^ in men and women, respectively.^55^

#### Data collected at baseline and 3 and 6 months’ follow-up

Follow-up data will be collected by the researchers by telephone at 3 and 6 months after recruitment (table 1) and include:

*Functional status*: Barthel score will be collected from each participant at 6 months’ follow-up.^41^*Resource usage*: Data collected at 3 and 6 months from different sources will inform which to use in the future trial. Sources include: a short questionnaire (modified version of the client service receipt inventory) on social and personal expenditure self-reported by participants at baseline, and 3 and 6 months which will be verified by extracting information about healthcare service usage from the hospital PAS and primary healthcare systems such as TPP SystmOne.*Quality of life*: EQ-5D-5L and ICECAP-O will be collected at 3 and 6 months.*Acceptability of the assessments for frailty and sarcopenia*: The views and experience of patients and staff of assessing frailty and sarcopenia in fracture clinics will be obtained using qualitative semistructured interviews. Semistructured interview guides have been codesigned with PPI researchers. Purposive sampling will be used to select: (1) patients (n=15–20) who completed frailty and sarcopenia assessments to include men and women with and without frailty and/or sarcopenia; (2) staff (n=5–8) including consultants and nurses involved in providing the care to patients in fracture clinics; and (3) staff (n=5–8) including consultant geriatricians, frailty practitioners and therapists from local geriatric clinical services. Interviews with patients will take place soon after enrolment to the study to maximise recall. Interviews will take place in the participants’ own homes and are anticipated to last for 30 min. Staff interviews will take place later in the recruitment period to capture how the additional assessments and referrals impacted on workload and service provision. All potential participants will receive an interview-specific information sheet and will be allowed at least 24 hours to decide whether to take part in the interview. Explicit written consent will be obtained from each participant prior to the interview. All interviews will be audio recorded using a digital recorder and will be transcribed for later analysis.

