**Methods and analysis:**

This study will be conducted in three fracture clinics in one acute trust in England. 100 people aged 65+ years with an upper arm fracture will be recruited and assessed using six validated frailty measures and two sarcopenia tools. The prevalence of the two conditions and the best tools to use will be determined. Those with either condition will be referred to geriatric clinical teams for comprehensive geriatric assessment (CGA). We will document the proportion who are referred for CGA and those who receive CGA. Other outcome measures including falls, fractures and healthcare resource use over 6 months will be collected. In-depth interviews with a purposive sample of patients who undergo the frailty and sarcopenia assessments and healthcare professionals in fracture clinics and geriatric services will be carried out to their acceptability of assessing frailty and sarcopenia in a busy environment.

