Despite the increasing evidence for the association of fractures with frailty and sarcopenia, the two conditions remain under-recognised and therefore undertreated in patients with fragility fractures.^26 33^ Exercise and adequate nutrition, particularly with regard to vitamin D, calcium and protein, are key lifestyle approaches that can optimise bone, muscle and functional outcomes in older people, if they are individually tailored and appropriately prescribed.^27 34^

Early identification and treatment of sarcopenia has been suggested to be an important element in the future prevention of fractures.^35 36^ Comprehensive geriatric assessment (CGA)—a method of identifying and treating an older person’s medical, functional and psychosocial problems by multidisciplinary health and social care teams—can offer an opportunity to manage these age-related syndromes and improve health outcomes.^37^ A recent study has reported that CGA can help identify those with an increased risk of hip fractures allowing the implementation of prevention strategies.^38^ The aim of this study is to evaluate the feasibility of assessing people aged 65+ years, who attend fracture clinic with an upper limb fracture, for frailty and sarcopenia in addition to routine assessment for fracture risk due to osteoporosis. We will demonstrate whether it is practical and acceptable (to patients and staff) to assess for frailty and sarcopenia in a busy fracture clinic typical of those found in every general hospital, and then further manage these patients through geriatric clinical services. This feasibility study will inform a future randomised controlled trial.

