## Methods and analysis

### Study objectives

Evaluate the feasibility of assessing patients for frailty and sarcopenia in a busy fracture clinic.Evaluate the feasibility of using existing CGA care pathways following assessments for frailty and sarcopenia.Determine the views of clinicians and patients on the acceptability of the assessments for frailty and sarcopenia and availability of current care pathways.Decide which outcomes to use for a future randomised controlled trial.Estimate the key resource usage of the intervention including those associated with referrals coming from the CGA process.

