### Feasibility outcomes

*Feasibility of assessing frailty and sarcopenia among patients with upper limb fracture*: This will be determined by: (A) the percentage of people who are assessed by each tool (adequacy); (B) availability of required data and the number of missing data; (C) equipment (including cost, availability of functioning equipment and frequency of calibration); (D) the time for carrying out each assessment; and (E) acceptability of the tools by staff and patients (via interviews). This will determine the prevalence of frailty and sarcopenia among the study participants and which measures of assessing frailty and sarcopenia are most feasible in this population*Feasibility of using existing care pathways*: Patients identified as having either frailty or sarcopenia will be referred to local geriatric clinical services for specialist review as outlined in the intervention. The actions instigated from these assessments and referrals will be varied and individualised according to patient’s needs and wishes. These referrals may lead to additional attendance at outpatients, primary care or exercise classes, for example. We will report the number of patients identified to have frailty and/or sarcopenia who are referred to CGA, the number of those who receive CGA and the number and type of follow-up interventions.*Falls and fractures*: Participants will be asked to fill in a falls diary recording the date, suspected cause, location and the consequences of each fall. They will be contacted by telephone at 3 and 6 months after recruitment to collect self-assessed information on falls and fractures within the previous 3 months. This will establish whether quarterly data collection is suitable for the future trial.*Mortality*: Death rates within 6 months of recruitment will be collected from the hospital patient administration system (PAS).*Future outcome measures*: Baseline data on nutritional, physical and cognitive factors which may be associated with frailty and sarcopenia status will be collected. Quality of life and physical function will be measured at baseline, and 3 and 6 months after recruitment. The feasibility of using each of these assessments in this patient group will inform which instrument will be used in the future trial.*Healthcare resource use*: Testing the key resource usage of the intervention and downstream influence on service usage including those associated with referrals coming from the CGA process.*Quality of life*: Quality of life will be measured by EuroQual-5 dimensions-5 levels (EQ-5D-5L) and ICEpop CAPability measure for Older people (ICECAP-O). We will explore which instruments will be more sensitive in measuring quality of life changes for our study population and how often we should collect such information.

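### Patient interviews are drawn from completers and held early, so patients' accounts of unfinished tools and of the care pathway are likely to be thin

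*Protocol article*

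**What the plan says.** The section on data collected at baseline and follow-up defines the patient interview sample as "patients (n=15–20) who completed frailty and sarcopenia assessments to include men and women with and without frailty and/or sarcopenia". The sampling characteristics it names are sex and frailty or sarcopenia status; completion and referral are not among them. The abstract is looser and speaks of "In-depth interviews with a purposive sample of patients who undergo the frailty and sarcopenia assessments".

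On timing, the same section states: "Interviews with patients will take place soon after enrolment to the study to maximise recall". It describes no later patient interview. Staff are treated differently: "Staff interviews will take place later in the recruitment period to capture how the additional assessments and referrals impacted on workload and service provision".

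The third study objective is: "Determine the views of clinicians and patients on the acceptability of the assessments for frailty and sarcopenia and availability of current care pathways". The aim, at the end of the Introduction, asks whether it is practical and acceptable to patients and staff to assess for the two conditions "and then further manage these patients through geriatric clinical services". Under Feasibility outcomes, item (E) is "acceptability of the tools by staff and patients (via interviews"), and the Quantitative data analysis section again takes acceptability from interview data when each measure is judged.

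**The concern.** There are two mismatches between what is asked and who is interviewed, and when.

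First, a participant who declined a tool or could not finish it is the person best placed to say what made it unacceptable. This is a realistic case here. The baseline battery includes grip strength, repeated chair rises and bioimpedance with a wrist electrode, in people aged 65 or over with a recent wrist or upper-arm fracture. If interviews reach only completers, the study learns how many did not finish but not, from the patients, why.

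Second, referral and CGA follow the baseline assessment. A patient interviewed shortly after enrolment may have little to say about the pathway, yet the objective and the aim include patients among those whose views are sought.

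The study is meant to choose tools and outcomes for a randomised trial. If completion is poor, the Progression criteria ask the Trial Steering Committee to consider practical changes that would raise it. Patients' reasons for not completing are what that discussion would need.

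**Working it through.** No calculation is attached to the 15–20 interviews, so there is no figure of the plan's to reproduce. The check sets the sections side by side.

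**Part 1: who is interviewed**

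1. The operative sampling rule (follow-up data section) requires completed assessments. The abstract requires only that patients undergo them. The two differ for anyone who started but did not finish.
2. Interviews are the only stated source of acceptability (Feasibility outcomes, item E; Quantitative data analysis).
3. Other measures do include non-completers: the percentage assessed by each tool, missing data and time taken (Feasibility outcomes, items A, B and D), the completion threshold (Progression criteria) and the reported completion rates. These are counts and times. None is described as recording a reason.
4. Respondent validation (Qualitative data analysis) returns to people already interviewed, so it brings in no one new.

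As an illustration of how the lean would scale, let c be the share completing, and let A_c and A_n be acceptability among completers and non-completers. Then

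- acceptability in everyone = c·A_c + (1 − c)·A_n
- overstatement from hearing completers only = A_c − [c·A_c + (1 − c)·A_n] = (1 − c)·D, where D = A_c − A_n.

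D is an assumption; the document gives no value.

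| c | D = 0 | D = 10 points | D = 20 points | D = 40 points |
|---|---|---|---|---|
| 50% | 0 | 5 | 10 | 20 |
| 80% | 0 | 2 | 4 | 8 |
| 100% | 0 | 0 | 0 | 0 |

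The 50% row is the lowest completion that does not trip the progression rule. It is not a forecast. Purposive interviews analysed thematically do not estimate a proportion, so the table shows only the direction and what drives it.

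**Part 2: when they are interviewed**

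1. Referral to geriatric services follows identification at the baseline assessment (Intervention; Feasibility outcomes).
2. Patient interviews come soon after enrolment. Neither that interval nor the wait for geriatric review is stated, so the overlap cannot be computed.
3. In the same section, staff interviews are placed later so that the effect of referrals can be seen. The protocol therefore accepts that learning about referral takes time.
4. Patient-side pathway data are otherwise counts: referred, received CGA, and number and type of follow-up interventions (Feasibility outcomes). The 3- and 6-month items in Table 1 and the follow-up section contain no pathway views.

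**The case against.** The strongest reply is that too much is being hung on one word. With eight tools in the battery, having completed the assessments may mean no more than having attended the session, which is how the abstract reads. Someone who refused one tool could then be interviewed. This stands as far as it goes: the wording is ambiguous, and exclusion follows only from reading the operative rule literally. Even on the generous reading, nothing ensures that such people are sampled.

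A reader might also infer that tool choice will favour long physical tools that others could not finish. The documents do not support that. A long or often failed tool is marked down on time and missing data, and fracture-clinic staff, who are also interviewed, can report refusals and difficulties. What is lost is the patient's own account.

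On timing, early interviews have a stated and sensible purpose, which is recall of the assessments. Objective 3 refers to the availability of pathways, not the acceptability of CGA, and staff from geriatric services can speak to availability. Objective 2, the feasibility of the pathway, is served by the counts. All of this stands. What remains is that objective 3 names patients as well as clinicians, and the aim couples acceptability to patients with onward management.

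Finally, the interview guides are not shown, and they may include questions about referral. They could not supply experience that patients have not yet had.

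**Conclusion.** The point holds as a moderate mismatch between objective and method, and it is worth correcting because correction is cheap. Interview-based acceptability probably leans favourable. That is the expected direction, not a demonstrated result, and it assumes that the sampling rule is applied as written, that some participants do not finish, and that they view the tools less favourably than those who do. If nearly everyone completes, the first part has little effect.

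Three stronger readings should be avoided. It does not follow that half the participants will be outside the interview frame, because 50% is a threshold for declaring the assessments not feasible. It does not follow that the patient part of objective 3 is unanswerable, because the interval to interview and the wait for CGA are both unstated and some interviewees may already have been referred. Nor does the study lose sight of non-completers: they are counted, but their reasons are not sought.

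**What to change.** - Keep 15–20 patient interviews, but sample from all consented participants who began the assessments, and use the same wording in the abstract and the methods. Reserve a few places for people with at least one refused or incomplete tool.
- Record a coded reason for every tool not completed.
- Keep the early interviews for recall of the assessments. For referred participants, add a few open questions about referral and the care pathway to the existing 3- and 6-month telephone calls. Alternatively, restrict the pathway part of objective 3 to clinicians, and word the aim to match.

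The cost is a few fewer interviews with completers, a few more minutes on calls that are already scheduled, and a minor ethics amendment.

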#### Study progress

Participant recruitment started in March 2019 and will finish in March 2020.

## Data analysis

### Quantitative data analysis

Data will be double entered onto an SPSS 22 database and participants will be identified only by a study ID number. In line with good practice,^56^ the feasibility outcomes will be reported descriptively and narratively. Numbers and characteristics of participants recruited will be summarised using appropriate descriptive statistics. The prevalence of frailty and sarcopenia will be calculated for each measure and reported with 95% CIs. Agreement between measures will be examined using Cohen’s kappa statistics. The feasibility and practicality of each frailty and sarcopenia measure will be examined according to the number of missing variables, the time required to complete them and their acceptability to staff and patients (from interview data).

The clinical outcomes, including falls and fractures as well as mortality rates, will be reported as descriptive statistics (counts (%), mean and median) with 95% CIs at each follow-up time point. Descriptive summaries of changes in clinical outcomes, physical function (Barthel score) and quality of life between baseline and 6 months’ follow-up will be presented.

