### Recruitment

Eligible patients identified by the fracture clinic team using electronic records will be sent an invitation letter and study information sheet prior to their clinic appointment, typically a few weeks after their fracture. Patients will have at least 24 hours to consider whether they would like to take part and the opportunity to discuss the study with a researcher on arrival at the clinic. Informed written consent will be obtained from all participants.

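### The planned baseline-to-6-month change in falls, fractures and mortality compares unlike quantities, and the change in function and quality of life includes recovery from the injury

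*Protocol article*

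**What the plan says.** All references are to the Protocol article.

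- **Planned analysis (Quantitative data analysis).** The outcomes are set out first: "The clinical outcomes, including falls and fractures as well as mortality rates, will be reported as descriptive statistics", with confidence intervals at each follow-up point. The next sentence adds "Descriptive summaries of changes in clinical outcomes, physical function (Barthel score) and quality of life between baseline and 6" months.
- **Baseline events (Baseline data).** The item reads "Number of falls in the previous years, number and type of fractures". The number of years is not fixed, fractures have no window, and nothing says whether the index fall or fracture counts.
- **Follow-up events (Feasibility outcomes).** Participants are telephoned at 3 and 6 months "to collect self-assessed information on falls and fractures within the previous 3 months". They also keep a diary in which each fall is dated. Deaths are those within 6 months of recruitment.
- **Entry (Setting and participants; Recruitment).** Every participant has a single arm fracture. The clinic visit is "typically a few weeks after their fracture".
- **Function and quality of life.** Feasibility outcomes says: "Quality of life and physical function will be measured at baseline, and 3 and 6 months after recruitment". The follow-up section says "Barthel score will be collected from each participant at 6 months" and lists no 3-month Barthel. Table 1 marks Barthel at baseline and 6 months only, and gait speed, grip strength and chair rise at baseline only. EQ-5D-5L and ICECAP-O are marked at all three points.

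**The concern.** A change score is interpretable only if both ends measure the same thing over the same length of time. For falls and fractures they do not. The baseline looks back over a longer, undefined period that may contain the event that brought the patient into the study. The follow-up is short and starts after that event. For mortality there is nothing to subtract from. A summary that follows the text can therefore show fewer falls and fractures when risk has not moved.

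Barthel, EQ-5D-5L and ICECAP-O raise a different issue. They record current state, but the first reading comes soon after an injury, there is no control group, and collection moves from in person to telephone. Recovery from the fracture cannot be separated from anything that comprehensive geriatric assessment (CGA) does.

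The stakes lie in how the results are used. One study objective is to choose outcomes for the future trial, and the protocol intends to explore which quality-of-life instrument is more sensitive to change. An instrument that mainly registers recovery from the fracture could be taken as sensitive to CGA.

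**Working it through.** The protocol gives no figure for any of these changes, so there is none to reproduce. Its sample-size statement concerns the precision of a prevalence and does not enter here. The check asks what the planned comparison would show if underlying risk did not change.

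**Inputs**
- Proportion falling per year: 35% (Abstract). The Introduction gives a third overall and 50% above age 80, so 33% to 50% is used as a range.
- Fractures: 10–15% (Abstract), read as a share of those who fall.
- Follow-up window: 3 months per call, 6 months for both calls together.
- Baseline window: not fixed. **Assumed** 12 months, with 24 months as a variant.
- Constant risk over time (assumed).

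**1. Falls: effect of the window alone**

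At a constant rate the expected count is proportional to window length.
- 12 v 6 months: 6/12 = 0.50, a count 50% lower.
- 12 v 3 months: 3/12 = 0.25, 75% lower.
- 24 v 6 months: 6/24 = 0.25, 75% lower.

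These ratios depend neither on the fall rate nor on counting the index event. With rate λ = −ln(1 − 0.35) = 0.431 per person-year:

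| Window | Mean falls | Any fall |
|---|---|---|
| Baseline, 12 months, index fall not counted | 0.43 | 35% |
| Baseline, 12 months, index fall counted, if every index fracture came from a fall | 1.43 | 100% |
| Follow-up, both calls (6 months) | 0.22 | 1 − 0.65^0.5 = 19.4% |
| Follow-up, one call (3 months) | 0.11 | 1 − 0.65^0.25 = 10.2% |

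For annual proportions of 33% to 50%, any fall is 18.1–29.3% over 6 months and 9.5–15.9% over 3 months.

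**2. Fractures: effect of counting the index event**

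Annual risk is 0.35 × 0.10 = 3.5% to 0.35 × 0.15 = 5.25%.
- 6 months: 1 − (1 − 0.035)^0.5 = 1.8% to 1 − (1 − 0.0525)^0.5 = 2.7%.
- 3 months: 1 − (1 − 0.035)^0.25 = 0.9% to 1 − (1 − 0.0525)^0.25 = 1.3%.
- At three times that annual risk (10.5% to 15.75%), 6 months gives 5.4% to 8.2%.

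If the index fracture is counted, baseline is 100% by eligibility. The comparison is then 100% against about 2–3%, and still against only about 5–8% at triple the risk. If it is not counted, the size cannot be computed, because the baseline item has no window.

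**3. Mortality**

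Everyone is alive at recruitment, so a change from baseline only restates the 6-month proportion.

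**4. Function and quality of life**

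The protocol gives no values from which to compute a change. The instruments have no look-back count to inflate. What can be said is that the baseline follows the injury, no pre-injury reading is planned and there is no comparison group.

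**5. Schedule**

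Feasibility outcomes promises physical function at 3 months. Table 1 and the follow-up section schedule no physical function measure then. Both cannot be right.

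**The case against.** The strongest reply is that little depends on these summaries. They are descriptive, in a feasibility study, with no test or efficacy claim attached. The progression criteria use prevalence, completion of assessments and recruitment. Falls, fractures and deaths are also reported on their own at each follow-up point, which the baseline problem does not touch, and the dated diary allows interval rates to be derived. Whether the index event counts could be settled in a case report form or in the full protocol. All of this stands. It limits the severity, but it does not make the stated change summary meaningful.

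It is also fair that 75% is the less favourable comparison. The planned interval is 6 months and the two calls together cover it, so 50% is the natural figure under the 12-month assumption.

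A reader might infer that every planned change is improvement by construction, function and quality of life included. The document does not support that. Those instruments measure current state; recovery is expected, but a ceiling or a decline is possible. A reader might also take a near-total drop in fractures as certain. That requires counting the index fracture, on which the document is silent. Similarly, the Introduction says only that such fractures often follow a low-energy fall, so a 100% baseline for falls is an upper bound.

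**Conclusion.** The point holds for falls, fractures and mortality: baseline and follow-up are not on a common footing. With no change in risk, the fall count would be 50% lower over both calls, or 75% lower over one, assuming a 12-month look-back; a longer look-back widens the gap. The fracture contrast, 100% to about 2–3% over 6 months, is conditional on counting the index fracture and on the background rates in the Abstract.

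For Barthel, EQ-5D-5L and ICECAP-O the conclusion is narrower. Change includes recovery from the injury by an amount the protocol does not allow one to estimate. It should not be read as a pathway effect or as sensitivity to CGA.

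The conflict over 3-month physical function is plain on the face of the text and rests on no assumption.

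Severity is moderate. The fault could mislead outcome and instrument choice. A reader might infer that it undermines the decision to proceed or a planned effect size, but the progression criteria do not use these changes and the document attaches no effect-size calculation to them.

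**What to change.** 1. **Falls, fractures, deaths.** Drop change from baseline. Report post-recruitment falls and fractures as rates per person-time over 0–3, 3–6 and 0–6 months with 95% CIs, counting only time covered by a completed call or diary. Report deaths as a proportion with its CI.
2. **If a baseline rate is shown.** Fix the look-back length, exclude the index fall and fracture, and express both periods on the same time scale.
3. **Barthel, EQ-5D-5L, ICECAP-O.** Show every time point collected. State that change includes injury recovery and is not evidence of a pathway effect or of instrument sensitivity to CGA.
4. **Schedule.** Reconcile Feasibility outcomes with Table 1 and the follow-up section, for example by collecting Barthel at the 3-month call already planned or by correcting the text.

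Items 1 to 3 are mainly analysis wording, although fixing the look-back may also need a clearer baseline question. Item 4 costs at most one score at an existing call. Recruitment began in March 2019, so participants already past that call would lack it, and the change may need ethics approval.

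A recalled pre-fracture rating of function and quality of life is optional and not part of the required fix. It adds recall error and burden, and would be missing for those already enrolled.
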